## Methods: Data Collection, Management, And Analysis

### Saccade Function Testing

During the week prior to and the week following the intervention period, participants will be tested for both voluntary and reflexive saccade performance (see Table 6 for summary of saccade testing). Voluntary saccade testing will involve the same task as the training sessions, in the 10°, 20°, and 30° amplitudes only. In the reflexive saccade testing session, the same amplitudes will be tested following the reflexive testing protocol. As in the voluntary saccade testing, each amplitude will be tested for the eight cardinal and intercardinal directions. Five trials will be performed per direction, resulting in 40 trials per amplitude in a testing session. The structure of each trial consisted of the initial fixation period, followed by the simultaneous disappearance of the central fixation target and appearance of the reflexive target, and finally the resetting period. Unlike in the voluntary saccade trials, there is no presentation of the circle of targets prior to the appearance of the reflexive target and no arrow to indicate the direction of movement to be performed (see Figure 3). Assessments will begin with a warm-up for the eyes in order to minimize the risk of injury. Participants with no known neurological disorders (see Supplementary Material Data Sheet 2 sample physician release form) will complete only the eye-tracking related assessments. There will be one pre-training assessment and one post-training assessment, totaling two assessment periods for the control group protocol. Each assessment period should last no longer than 1.5 h including rest periods.

**Table 5 T5:** Investigator team activity timeline.

			Approximate	Prestudy	Basline/			Intervention
	PD Only		time to	screening/	Intervention	Intervention	Intervention	week 4/
Activity/assessment	(Yes/	No)	Staff member	complete	(min)	consent	week 1	week 2	week 3	conclusion
Prescreening consent		Study coordinator	5	X				
Screening checklist		Study coordinator	10	X				
Consent form		Study coordinator	45	X				
Medical release and relevant medical history	Yes	Potential participant’s neurologist	30	X				
Hoehn and Yahr scale	Yes	Clinical assessors	30		X			
Montreal Cognitive Assessment	Yes	Clinical assessors	30		X			
Unified Parkinson’s Disease Rating Scale	Yes	Clinical assessors	30		X			
Voluntary saccade assessment		Staff member	45		X			
Reflexive saccade assessment		Staff member	45		X			
Voluntary saccade training intervention		Staff member	45		X X	X X	X X	X X
Termination form		Study coordinator	N/A					X
Serious adverse event form		Study coordinator	N/A	As needed throughout protocol		
Progress note		All team members	N/A	X	X	X	X	X
Communication log		All team members	N/A	Every phone or in-person contact outside of regular study visits		

**Table 6 T6:** Saccade testing summary table.

VOLUNTARY	REFLEXIVE
**Amplitudes**: 10°, 20°, and 30°	**Amplitudes**: 10°, 20°, and 30°
**Directions (*Cardinal*):** North, Northwest, West,	**Directions (*Cardinal*):** North, Northwest, West,
Southwest, South, Southeast, East, Northeast [8 total]	Southwest, South, Southeast, East, Northeast [8 total]
**Repetitions PER Direction**: 5×	**Repetitions PER Direction**: 5×
**Total Trials**: 120	**Total Trials**: 120
**Task**: Voluntary Saccade	**Task**: Reflexive Saccade

*Combination of voluntary and reflexive eye-tracking related assessments will last approximately 1.5 h including rest time*.

Participants will perform eye-tracking related assessments in ON and OFF motor-related medication states in order to completely characterize the effects of eye-movement training in PD (see Table 7 for OFF-state timeline). Participants will continue regular intake of any medications that are unrelated to motor symptoms in PD.

**Table 7 T7:** OFF-state testing timeline for participants.

Night Before	7:00 AM	8:30 AM	9:00 AM	10:00 AM
Take last dose of medication at 11 PM (taken 8 h before morning assessment)	Eye-Tracking Assessment (OFF-state)	MDS-UPDRS Assessment	**RETURN TO MEDICATION (60-min break)**	Eye-Tracking Assessment (ON-state)

### Clinical Mobility Testing for Participants With Parkinson’s

Following completion of eye-tracking related assessments, the participant’s motor function will be assessed using the Movement Disorder Society-United Parkinson’s Disease Rating Scale (MDS-UPDRS) in the OFF-state for an accurate description of PD stage. To achieve the OFF-state, participants will be instructed to take their last dose of medication approximately 8 h before their scheduled morning assessment. This approach will time the initiation of the OFF-state with the beginning of data collection. Immediately following the OFF-state eye-tracking assessment, the MDS-UPDRS will be administered to participants in the NDHD Laboratory which is equipped with ballet barres for support. Immediately after the MDS-UPDRS administration, participants will be instructed to take their medication and take a 60 min long break while they return to their normal ON-state. This protocol will mitigate the time spent in the OFF-state to approximately 2 h. Sixty-minutes after the intake of medication, participants will complete a final eye-tracking assessment in the ON-state. In total, pre/post-assessments will last at most 4 and a half hours, including the 60 min break and assessment beaks. A summary of an example Parkinson’s pre-training and post-training assessment timeline follows: If the participant takes medications in a schedule other than every 8 h, the participant will time the start of the experiment with their regular time of medication intake and withhold from taking their regular dosage for the first 2 h of the experiment. After those 2 h, the participant will resume regular medication intake.

### Processing

Eye tracking data for both the left and right eyes is first converted to ASCII files, which will be then converted into two types of ASCII files: gaze data, which consisted of pupil position relative to the room, and head referenced (*href*) data, which consists of pupil position relative to the head. In order to minimize false positive detection of saccades caused by head movement, the *href* data is then used for further processing. This data is then processed in MATLAB (MathWorks, Inc., Natick, MA, United States) using a program developed by [name]. This program converts eye tracking data from pixel measurements of movement distances to radial distance based on the fixed distance of the participant from the experiment display. The program also uses median pupil position during fixation to find the center of the visual focus for each trial to calculate real saccade distances, removing the assumption that the center of the visual fixation target is the center of actual fixation. Blinks and their subsequent movements will be detected and removed using a data-driven blink finder in the MATLAB program. Saccade latency is calculated as the time between presentation of the directional arrow and the first eye movement crossing the velocity threshold of 30°/s and the acceleration threshold of 8000°/s^2^, as specified by the EyeLink^^®^^ II User Manual (Jainta et al., 2011). The program then removed faulty fixations and appended the start of each saccade to occur 1.6 ms after the end of the previous fixation. This auto-cleaned data will be then stored and plotted, allowing the data to be visualized for each trial and cleaned on a per trial basis using an additional section of the MATLAB script edited by the user. This script allows users to, on either eye, delete trials missing excessive position data or delete false saccades not detected by the automated cleaning process. Additionally, users could shift the start and/or end of a fixation to match visually determined correct times based on the plot of radial position versus time. Saccades are automatically shifted along with the endpoints for adjusted fixations. The user can also move individual saccades and insert fixation-saccade pairs to match visually determined significant pupil movements. Only the first three saccades in each trial will be analyzed since this was a sufficient number of saccades to reach the target in preliminary tests.

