#### Secondary Outcome Measures

One secondary outcome for this study is Movement Disorder Society-sponsored new version of the Unified Parkinson’s Disease Rating Scale (MDS-UPDRS). The MDS-UPDRS assesses motor examination and complications, motor aspects of daily living, and non-motor aspects of daily living using a combination of questionnaire and task performance assessment (Goetz et al., 2008; Martinez-Martin et al., 2013). The MDS-UPDRS will only be assessed in participants with PD, as participants with no known neurological disorders should not present disability measurable with these instruments. Additionally, the peak saccadic velocity, duration, and amplitude will be analyzed as a measure of changes to the main sequence (Bahill et al., 1975).

Primary outcomes will be assessed by a member of the NDHD laboratory staff blinded to secondary outcome assessment, which will be performed on a separate day (see Table 5 for investigator team timeline). Secondary outcome assessors will be blinded to primary outcomes and will not be involved in training sessions. Changes after the four-week intervention from the initial value of each primary and secondary outcome measure will be analyzed using an ANOVA of mixed effects.

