### Statistical Methods

After data cleaning is completed using the automatic and user-guided portions of the MATLAB program, the cleaned data for all trials, which contains pupil position data for both eyes, will undergo statistical analysis. Using SAS, an ANOVA with mixed effects will be performed using the finalized data concerning four variables of interest for both voluntary and reflexive saccades: (1) normalized mean velocity, (2) normalized angular distance, (3) latency for the first saccade in a trial, and (4) saccade count to target (SAS Institute Inc., Cary, NC, United States). For participants with PD, the UPDRS scores before and after the intervention will be included with the eight saccade variables in the ANOVA with mixed effects to determine if any significant clinical mobility improvements occur. In secondary analyses, saccade-related measurements will be compared between the voluntary and reflexive saccades and by target amplitude. In the case of non-normality, non-parametric statistical methods will be used. Saccade data that are not viable for statistical analysis due to problems in recording eye movements, such as blinks obscuring saccades and loss of fovea tracking during a saccade initiation or endpoint, will not be included in the statistical analyses. Main sequence analysis will be included as a secondary form of analysis. Due to the comparatively weaker relationship seen between peak velocity and amplitude in the range that will be recorded, analysis of the relationship between mean velocity and amplitude and the relationship between duration and amplitude will be included (Bahill et al., 1975).

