Inclusion criteria: For participants with PD: (1) medically stable with diagnosis of PD by meeting the United Kingdom PD Society Brain Bank Criteria, (2) to have a Modified Hoehn & Yahr stage 1–2 (with unilateral involvement only, unilateral and axial involvement, and bilateral involvement without impairment of balance) in the conventionally defined OFF medication state, (3) to have medical clearance form from their physician for participation in the study, (4) to be in a stable regimen of PD medication 30 days prior to the initiation of the study and until the completion of the study, (5) to be willing and able to provide informed consent, (6) to be of age 40 and up, and (7) must have a caregiver/family member present for OFF-state assessment sessions.
For neurologically healthy participants: (1) no known neuromuscular disorders, (2) to have medical clearance form from their physician for participation in the study, (3) to be willing and able to provide informed consent, and 4) to be of age 40 and up.
Exclusion criteria: (1) presence of dementia based on The Montreal Cognitive Assessment (MOCA) –score of less than 25, (2) diagnosis of comorbid neurological disorder such as epilepsy, (3) history of neurological injury such as stroke, (4) history of brain surgery such as deep brain stimulation, (5) concurrent severe medical illness which in the opinion of the research team will preclude participation in the study (such illnesses may include but not limited to severe or uncontrolled cardiovascular disease, hypertension, pulmonary disease, or diabetes), (6) inability to attend and participate in at least seven of the training sessions, (7) uncorrected vision, history of retinal disease (e.g., macular degeneration), presence of optic neuropathy due to glaucoma or ischemic optic neuropathy, pseudoexfoliation syndrome, ocular surgery, ocular trauma, visually significant cataract, orbital myositis, blindness or refractive errors outside –5 to +3 D, (8) indication by the participant’s neurologist in the medical release form that testing the participant in the OFF-medication state would put PD participants at significant risk for medical complications.
Study type: Interventional
Allocation: no randomization; Intervention model: two-arm pre-post; Masking: non-masked
Primary purpose: eye movement training
Study Phase: Phase 0
Date of first enrolment: March 12, 2016
Target sample size: 44
Recruitment status: Recruiting

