### Access to Data

The final trial de-identified dataset will be available to members of the NDHD laboratory staff and stored in an online data repository. To minimize bias, investigators performing data processing of eye tracking data will not have access to clinical measure outcomes or identifying information until the end of the study. Similarly, clinical assessors will not have access to eye tracking data or other information that could bias assessment.

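### Eye-tracking records are edited by visual judgement before the primary analysis, and the stated masking of the people who process them does not cover visit or medication state and is unclear for group

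*Protocol article*

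**What the plan says.** All of this is in the protocol article.

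- **Automatic step.** Primary Outcome Measures and Processing fix saccade onset by a velocity threshold of 30°/s and an acceleration threshold of 8000°/s². The auto-cleaned data are stored and plotted.
- **Manual step.** Processing then lets a user "delete trials missing excessive position data or delete false saccades not detected by the automated cleaning process". It continues: "Additionally, users could shift the start and/or end of a fixation to match visually determined correct times", with saccades moving along with the fixation endpoints. Finally: "The user can also move individual saccades and insert fixation-saccade pairs to match visually determined significant pupil movements".
- **Use of the edited file.** Statistical Methods starts the analysis from this output: "After data cleaning is completed using the automatic and user-guided portions of the MATLAB program".
- **Masking.** Access to Data states that "investigators performing data processing of eye tracking data will not have access to clinical measure outcomes or identifying information until the end of the study". Secondary Outcome Measures blinds the primary-outcome assessor to the secondary assessment only. The registration data in Table 9 read "Masking: non-masked".
- **Coding.** Data Management and Confidentiality give each participant a code, and raw eye-tracking data are stored under the participant number.

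**The concern.** The four primary outcomes are first-saccade normalized amplitude, mean normalized velocity and latency, plus the number of saccades to target. Shifting a fixation endpoint moves the saccade, and so its latency. Moving, deleting or inserting a saccade can change which saccade is first, its size and duration, and the count. An objective onset rule is therefore open to override by eye.

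The research hypothesis is a greater pre-to-post improvement in PD than in controls. The labels that matter for an editor's expectations are therefore visit and group, and medication state for PD sessions. The safeguard in Access to Data is introduced as a way to minimize bias, yet it does not name any of these three. If editors do see them, small directional judgements could enter the contrasts the trial is meant to estimate. Collecting more trials reduces random error but leaves a systematic shift untouched.

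**Working it through.** The plan gives no figure to reproduce: no error rate for editing, no SD, and no alpha or power behind the sample size. The check has three parts.

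**1. What is masked, and to whom**

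- Clinical outcomes: hidden from data processors (Access to Data).
- Identity: hidden from data processors (Access to Data, with participant codes).
- Group: not named. Table 5 marks Hoehn & Yahr, MoCA and UPDRS as PD-only, so withholding clinical scores removes one cue to group. However, PD participants have OFF and ON eye-tracking sessions at each assessment (Table 7), so the number of files could itself indicate group.
- Visit: not named. A participant code does not by itself hide pre or post.
- Medication state: not named.
- Other sources of knowledge: only secondary-outcome assessors are kept out of training sessions (Secondary Outcome Measures). Table 5 assigns both saccade assessment and training to a generic staff member.

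**2. Size of a directional edit**

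If a share f of trials in one group at one visit is shifted by s on average, the mean for that group and visit moves by f × s, whatever the number of trials. Then:

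- bias in within-group change: B = (f × s at post) − (f × s at pre)
- bias in the PD-versus-control contrast: B(PD) − B(control)

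Assumed inputs, not from the documents: f = 10% to 30% and s = 10 to 40 ms for latency; one saccade added or removed in 5% to 10% of trials for the count.

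- Latency, editing at one visit only: 0.10 × 10 = 1 ms to 0.30 × 40 = 12 ms of bias in within-group change.
- Latency, same editing at both visits: 12 − 12 = 0 within the group.
- Latency contrast, both groups edited alike: 12 − 12 = 0.
- Latency contrast, only one group edited at one visit: up to 12 − 0 = 12 ms.
- Count: 0.05 × 1 = 0.05 to 0.10 × 1 = 0.10 within a group, so 0 to 0.10 in the contrast.

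The upper ends illustrate one-group, one-visit editing. They are not bounds.

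**3. What a bias would do to a test**

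Assumptions: true effect zero, two-sided alpha 0.05, normal test, and bias b in SDs of the change score. The Sample Size section gives 10% attrition, so 22 × 0.9 = 19.8, taken as n = 20 per group.

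Rejection probability = Φ(b/SE − 1.96) + Φ(−b/SE − 1.96), with SE = √(2/20) = 0.316 between groups and √(1/20) = 0.224 within a group.

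| Bias b (SD) | Between groups | Within group |
|---|---|---|
| 0 | 5% | 5% |
| 0.1 | 6% | 7% |
| 0.25 | 12% | 20% |
| 0.5 | 35% | 61% |

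For the between-groups column, b is the difference in editing bias between the groups. The milliseconds in part 2 cannot be placed on this scale because the documents give no SD.

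**The case against.** The strongest reply is that silence is not exposure. Nothing in the article says editors see visit, group or medication state. Identifying information is withheld expressly to limit bias, raw data are stored by number, and the code and proof of diagnosis are locked away. How files are labelled for cleaning could sit in a fuller document. The registry entry is a single field for a non-randomized study in which everyone receives the same training. It sits beside blinding statements elsewhere, so it cannot be a full account of who is masked. This much stands: the labels cannot be said to be visible, and group may be partly hidden.

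Two further points also stand. Deletion is not unrestricted. It is nominally limited to trials with too much missing position data and to false saccades, although no threshold is set. And directional editing that is equal in both groups cancels in the PD-versus-control contrast.

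The reply does not remove the point. The article does state a safeguard for data processors, and what it lists omits visit and medication state. For clinical assessors the same section adds a wider clause covering other information that could bias them; it does not extend that clause to those who edit the eye-tracking data.

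**Conclusion.** The concern holds as a risk that the stated safeguard leaves open. Visual editing can alter every primary outcome and feeds the primary analysis, while masking to visit and ON/OFF state is not stated and masking to group is unclear. With the assumed editing rates, bias in the PD-versus-control contrast runs from 0 to about 12 ms in latency or 0.10 in saccade count. Within-group change can be biased by editing that differs by visit alone. Whether these amounts matter cannot be judged without an SD.

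A reader might infer that editors know group and visit, and that hand editing will therefore manufacture the training effect. The documents do not support that. Exposure is inferred from what the masking statements leave out, and a false group difference needs editing that differs by both group and visit.

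A separate inconsistency should not be counted as support. Secondary Outcome Measures says of the secondary assessment, "which will be performed on a separate day", while Clinical Mobility Testing says "Immediately following the OFF-state eye-tracking assessment, the MDS-UPDRS will be administered", and Table 7 places both on one morning. That bears on masking between the two kinds of assessor, not on hand editing.

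**What to change.** Amend Processing and Access to Data as follows.

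1. Before manual cleaning, recode each session file with a random ID that hides participant, group, visit and medication state, and clean the files in shuffled order.
2. Have an existing team member who does not clean data hold the key until the cleaned dataset is locked.
3. Log every edit and deletion, and report the rates by group and visit.
4. Repeat the primary analysis on the stored auto-cleaned data as a sensitivity analysis.

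This needs no extra visits or participants. The cost is some scripting and logging, one further analysis run, and re-cleaning of any sessions already edited unmasked. Enrolment began in March 2016 and the article does not say how much has been cleaned, so that last item could be small or substantial.

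Separately, reconcile the timing of the secondary assessment in Secondary Outcome Measures with Clinical Mobility Testing and Table 7.

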### Data Management

All participants will be assigned a code for de-identification for all data collected. The participant code will be stored in a locked cabinet and destroyed when the study procedures are completed. Data analyses will be conducted on the coded non-identifiable data. All data will be kept in a locked file cabinet or in encrypted, password protected research computers. We will retain all screening data for those who qualify and volunteer and destroy the screening data for those who are excluded or do not choose to participate in the study. The informed consent, medical clearance, and verification of PD diagnosis will be stored together in a locked cabinet.

### Statistical Methods

After data cleaning is completed using the automatic and user-guided portions of the MATLAB program, the cleaned data for all trials, which contains pupil position data for both eyes, will undergo statistical analysis. Using SAS, an ANOVA with mixed effects will be performed using the finalized data concerning four variables of interest for both voluntary and reflexive saccades: (1) normalized mean velocity, (2) normalized angular distance, (3) latency for the first saccade in a trial, and (4) saccade count to target (SAS Institute Inc., Cary, NC, United States). For participants with PD, the UPDRS scores before and after the intervention will be included with the eight saccade variables in the ANOVA with mixed effects to determine if any significant clinical mobility improvements occur. In secondary analyses, saccade-related measurements will be compared between the voluntary and reflexive saccades and by target amplitude. In the case of non-normality, non-parametric statistical methods will be used. Saccade data that are not viable for statistical analysis due to problems in recording eye movements, such as blinks obscuring saccades and loss of fovea tracking during a saccade initiation or endpoint, will not be included in the statistical analyses. Main sequence analysis will be included as a secondary form of analysis. Due to the comparatively weaker relationship seen between peak velocity and amplitude in the range that will be recorded, analysis of the relationship between mean velocity and amplitude and the relationship between duration and amplitude will be included (Bahill et al., 1975).

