### Explanation for Choice of Comparators

There will be no comparator intervention used in this study. The effects of the voluntary saccade training intervention in persons with PD will be compared to those in persons with no known neurological disorders so that we can determine whether the group with PD is more responsive to the intervention. A greater response in the participants with PD would indicate a significant improvement in saccade performance. A lack of response to the intervention would indicate a resistance to improvement in saccade performance that may be characteristic of persons with PD.

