##### Secondary objectives

To determine whether training voluntary saccades affects motor disability in persons with PD. We will also investigate whether training voluntary saccades affects the relationship of the main sequence. Should statistical analysis reveal that these improvements are absent in participants with PD, we propose that saccade performance would be a potential early PD biomarker.

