#### Sample Size

There will be two groups with the same treatment: (1) a control group of participants with no known neurological disorders and (2) a test group comprised of participants with PD that have H&Y levels 1–2. In the absence of existing data in the literature to estimate the required same sample size for a protocol of this nature, the estimation is based on the number of eyes tested and trained in other eye movement studies and a 10% attrition rate seen in other studies performed by the authors (Hall et al., 2010; Knox and Wolohan, 2015; Ivanov et al., 2016; Heath et al., 2017).

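### The secondary objective asks whether training affects motor disability in PD, but MDS-UPDRS is measured only in trained PD participants, so a pre-post change cannot be attributed to training; the role of the saccade variables in its model also needs stating.

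*Protocol article*

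**What the plan says.** The protocol article's Secondary objectives set the question: "To determine whether training voluntary saccades affects motor disability in persons with PD".

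On who is measured, Secondary Outcome Measures states: "The MDS-UPDRS will only be assessed in participants with PD". On what they are compared with, Explanation for Choice of Comparators states: "There will be no comparator intervention used in this study". Sample Size adds: "There will be two groups with the same treatment".

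The analysis is described in two places:
- Statistical Methods first announces a mixed-effects ANOVA "concerning four variables of interest for both voluntary and reflexive saccades". It then says of the PD group: "the UPDRS scores before and after the intervention will be included with the eight saccade variables in the ANOVA with mixed effects". The stated purpose is "to determine if any significant clinical mobility improvements occur".
- Secondary Outcome Measures says that changes "from the initial value of each primary and secondary outcome measure will be analyzed using an ANOVA of mixed effects".

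**The concern.** There are two parts, and the first carries the weight.

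**Attribution.** An objective about what training does to motor disability needs some estimate of how MDS-UPDRS would have moved over the same weeks without training. The design offers none. The healthy group could not supply it even if scored, because it is trained too. Any movement from repeated testing, participants' expectations (the scale combines questionnaires with rated tasks) or rater drift goes straight into the estimate. A significant result would be reported as a mobility improvement from training, in the trial's only clinical outcome.

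**Model wording.** Statistical Methods does not say whether the eight saccade variables stand beside MDS-UPDRS as further outcomes or on the other side of the model as predictors. This matters because the Need for a Trial section proposes that better saccades may improve motor symptoms. On that account, saccade change lies on the pathway from training to motor benefit, and adjusting for it would remove the effect being sought.

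**Working it through.** **Figure in the plan.** None exists to reproduce. Sample Size gives no alpha, power, effect size or SD; 22 per group rests on precedent and 10% attrition.

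**Inputs from the document.** PD participants: 22 (Recruitment). Attrition: 10% (Sample Size). Completers: 22 × 0.90 = 19.8, taken as 20. Saccade variables: 4 measures × 2 saccade types = 8 (Statistical Methods).

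**Assumed inputs.** Two-sided test at 5%; drift and effects expressed in SDs of the individual change score; normal changes.

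**Step 1: uncontrolled drift with no training effect.** The paired t statistic has n − 1 = 19 degrees of freedom and non-centrality d × √n, where d is the drift in SDs. The critical value is 2.093.

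| Drift d | d × √20 | P(significant), n = 20 | P(significant), n = 22 |
|---|---|---|---|
| 0.2 | 0.894 | 0.136 | 0.146 |
| 0.3 | 1.342 | 0.247 | 0.269 |
| 0.5 | 2.236 | 0.5645 | 0.609 |

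A true training effect of the same size gives the same probabilities. The analysis has no means of telling the two apart.

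**Step 2: which model is described?** Set the places side by side.
- Abstract: mobility scores are listed in parallel with the saccade measures as things to be analysed by mixed-effects ANOVA.
- Secondary Outcome Measures: the change in each primary and each secondary outcome is analysed.
- Statistical Methods: the saccade measures are introduced as variables of interest, and the purpose clause treats mobility as the outcome.

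All three favour MDS-UPDRS as a ninth dependent variable analysed by the same method. Only the phrase that joins it to the eight saccade variables leaves another reading open.

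**Step 3: what the covariate reading would cost if an analyst took it.** Regress MDS-UPDRS change on an intercept and eight saccade changes, with n = 20. Residual degrees of freedom fall from 19 to 20 − 1 − 8 = 11. Further assumptions: each saccade change has mean 0.5 SD, pairwise correlation 0.3; true MDS-UPDRS change 0.66 SD, which an unadjusted paired test detects with 80% power; 8,000 simulated trials per row.

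| Share of effect running through saccades | Adjusted estimate (SD) | Power, adjusted |
|---|---|---|
| None | 0.66 | 38% |
| Half | 0.33 | 15% |
| All | 0.00 | 5% |

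These figures belong to that reading alone. With MDS-UPDRS as its own outcome there is no such loss, and Step 1 is the remaining problem.

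**The case against.** The strongest reply on the model is that the document largely answers the question itself. It never speaks of covariates, adjustment or a multivariate test, and the Abstract and Secondary Outcome Measures treat MDS-UPDRS as one outcome among several. An article also commonly leaves model specification to the analysis plan. This stands to a large extent. A reader of Statistical Methods alone might infer that the motor test must either be adjusted for its own mediators or pool nine variables with different units and directions of benefit, and so is uninterpretable. The documents do not support that: they offer a third, ordinary reading, under which the test is a valid estimate of within-group change. What remains is loose wording, worth one clarifying clause.

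On attribution, the reply is that this is openly an uncontrolled pre-post pilot with a secondary clinical outcome. There are also safeguards. PD medication must be stable throughout. MDS-UPDRS assessors are blinded to saccade results and take no part in training. Access to Data says they will not see other information that could bias assessment. These safeguards limit medication-related and rater drift. Blinding to visit is not stated, however, and the registration table lists masking as none. Nothing addresses retest or expectation in the participants. The pilot label does not turn a within-group change into an effect of training, and the objective is worded as an effect.

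**Conclusion.** The point holds in two parts of unequal weight.

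1. **Firm on every reading of the model.** The design cannot determine whether training affects motor disability in PD; it can only estimate how MDS-UPDRS changed in trained PD participants. As an illustration, assumed drift of 0.2 to 0.5 SD with 20 completers yields a significant change about 14% to 56% of the time with no training effect. The direction follows from the design. The size depends on the assumed drift, for which the documents give no value.
2. **A clarity point.** The role of the saccade variables is left open in Statistical Methods. The better-supported reading is sound. The covariate reading would shrink the estimate by whatever share of the effect runs through saccades and, under the assumptions in Step 3, cut power from 80% to between 38% and 5%.

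It would go too far to say that the stated model biases the clinical outcome, or that the outcome cannot be interpreted. Nor does anything here show that a particular MDS-UPDRS subscore has to be chosen.

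**What to change.** - **Secondary objectives:** reword to estimating the within-group change in MDS-UPDRS after training in persons with PD, without attributing it to training.
- **Statistical Methods:** align with Secondary Outcome Measures. State that MDS-UPDRS is its own dependent variable in a PD-only model with visit as fixed effect and participant as random effect, with no post-training saccade variables as covariates. Report the change as an estimate with a 95% interval.
- **Association with saccades:** present any relation between MDS-UPDRS change and saccade change as a separate, exploratory analysis.

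The cost is text only, with no change to recruitment, visits or measurements. The downside is a weaker mobility claim. Keeping the causal objective would instead require an untrained PD comparison group, which is a change of design.
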